### Procedure

All patients are screened by their treatment supervisors based on the in- and exclusion criteria. Patients who meet inclusion criteria are invited by an independent research assistant to participate, and receive an information letter (Fig. 3). Patients have 1 week to consider participation, after which written informed consent is obtained. Next, participants are randomly allocated to either VRAPT or waiting list condition and are monitored with the SDAS by staff for aggression on a weekly basis during 12 weeks before start of the intervention until the end of the follow-up. Before the intervention starts, pre-intervention measures are obtained (see Table 1). During 10 out of 16 sessions of VRAPT physiological measures of emotional arousal (i.e., heart rate and galvanic skin response) are measured. VRAPT consists of 16 bi-weekly individual sessions with a maximum duration of 60 min per session. The participants in the control condition will be placed on a waiting list. They will have the same assessments as the VRAPT group, i.e., the 32-weeks SDAS, pre-intervention, post-intervention and follow-up measurements. They will receive VRAPT after the last follow-up measurement. During the study period, for both conditions, treatment as usual will proceed, except for specific anger or aggression management therapy. During the intervention, aggression keeps being monitored with the SDAS by staff working on the ward. After the last session of the intervention, pre-intervention self-report measures are repeated in all participants, guided by assessors who are blinded for treatment allocation. During 12 weeks after end of the intervention, participants keep being monitored for aggressive behavior. Twelve weeks after the last session, self-report measures are repeated again.

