### Randomization

Participants will be randomly assigned to one of two conditions: VRAPT or waiting list. Randomization is conducted via a scientific randomization program on the Internet (https://www.randomizer.org), by the research coordinator of the Department of Psychiatry from the University Medical Center Groningen. Twenty-two sets consisting of two unique numbers are made available for each participating FPC. Research assistants are informed about the randomization by e-mail and communicate the condition verbally to the participants and the clinical teams.

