### Statistical analysis

Analysis of the data will be conducted according to the intention to treat principle [43]. The result of randomization will be checked by comparing baseline socio-demographic and clinical parameters between VRAPT and the waiting list condition, using univariate analyses (chi-square tests for dichotomous measures and t-tests for continuous measures). Differences in scores between pre-intervention, post-intervention and follow-up assessments and between intervention and control group will be examined for the dependent variables, using multilevel (repeated-measures) random linear regression analysis. Primary outcome measure is peak and general score as measured with the SDAS and self-report aggression measurement of participants. The SDAS and self-report measurement will be compared between VRAPT and waiting list, before, during and after VRAPT or waiting list. Effects of VRAPT will be tested with group x time interaction terms. Risk factors for aggression will be used as covariates in the linear regression models. Significance of fixed effects are assessed by Likelihood Ratio tests. Statistical significance of the regression effects will be tested using T-tests. In all analyses, a *p*-value < .05 will be considered statistically significant.

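### Randomisation comes before the 12-week SDAS baseline and the T1 questionnaires, and nothing withholds the allocation until they are complete, so the baselines of both primary measures may be unblinded

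*Protocol article*

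**What the plan says.** The Procedure section of the protocol article gives the sequence. After a week to consider and written consent, "Next, participants are randomly allocated to either VRAPT or waiting list condition and are monitored with the SDAS by staff for aggression", and this monitoring runs "on a weekly basis during 12 weeks before start of the intervention until the end of the follow-up". The questionnaires come afterwards: "Before the intervention starts, pre-intervention measures are obtained". Table 1 shows no SDAS rating before the 12-week observation period and no AVL before the pre-intervention visit.

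The Randomization section says: "Research assistants are informed about the randomization by e-mail and communicate the condition verbally to the participants and the clinical teams". It gives no time for this step.

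Under Design the trial is called single blind. The only blinding described (Procedure) is of the assessors who guide the repeated self-report measures after the intervention. The SDAS is scored by ward staff and the AVL is answered by the patient.

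The primary outcome is the SDAS peak and general scores together with self-reported aggression. On the test, the Statistical analysis section says: "Effects of VRAPT will be tested with group x time interaction terms". The same section plans to check the randomisation by comparing baseline socio-demographic and clinical parameters between the arms.

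**The concern.** A baseline is a safe reference level when it cannot have been influenced by the arm. Measuring it before allocation guarantees this, and so does concealing the allocation until it has been measured. As written, the plan does neither. Staff who score the SDAS over the 12 baseline weeks may know who is about to be trained. Patients filling in the AVL at T1 may know whether they are about to start or to wait. Both arms can live on the same ward (Waiting list section), so the same staff may rate patients of both arms.

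A group x time term compares later periods with the baseline period. If knowing the arm moves the baseline ratings and the movement then fades, the model reads the fading as a treatment effect or as harm, even if VRAPT does nothing. The balance check is also affected, but only for measures that can react to knowledge of the arm, such as SDAS and AVL. A difference there could be chance or a consequence of allocation. Socio-demographic comparisons are untouched.

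**Working it through.** **1. Does the SDAS baseline really fall after allocation?** The Procedure section speaks of "the 32-weeks SDAS, pre-intervention, post-intervention and follow-up measurements" for the waiting list, the same as for the VRAPT group. Adding the parts, with 16 sessions at two per week:

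12 baseline weeks + 16/2 training weeks + 12 follow-up weeks = 12 + 8 + 12 = 32.

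Reading bi-weekly as every two weeks would give 12 + 32 + 12 = 56, which does not match. The 12 baseline weeks therefore belong to the monitoring that the section lists after allocation. The SDAS section ties rating to inclusion criteria and consent, and asks for at least 12 weeks before training. It does not mention the date of randomisation, so it does not contradict this order.

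**2. The plan's own sample size.** Inputs from Power and sample size calculation: effect 0.5, power 0.80, two-sided alpha 0.05. The two-sample t-test needs 63.77, so 64 per arm, with power 0.801. The stated figure reproduces and is not in dispute; 64 per arm is used below.

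**3. What a baseline-only shift would do.** These inputs are assumptions, not figures from the document: no true effect; a difference s between arms, in SD units, present at baseline only and caused by knowing the arm; correlation ρ of 0.5 or 0.7 between baseline and outcome; equal SDs; a two-point comparison in place of the planned multilevel model.

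*Change contrast.* Bias = s. SE = √(2/64 × 2(1−ρ)), which is 0.177 for ρ = 0.5 and 0.137 for ρ = 0.7. The rejection rate is Φ(s/SE − 1.96) + Φ(−s/SE − 1.96). For s = 0.1 and ρ = 0.7, s/SE = 0.73, so Φ(−1.23) + Φ(−2.69) = 0.113.

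*Baseline-adjusted comparison.* Bias = ρs. SE = √(2/64 × (1−ρ²)), which is 0.153 for ρ = 0.5 and 0.126 for ρ = 0.7. The same rejection formula applies, with ρs in place of s.

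| s (SD) | ρ | Change: bias | Change: error | Adjusted: bias | Adjusted: error |
|---|---|---|---|---|---|
| 0.1 | 0.5 | 0.10 | 0.087 | 0.05 | 0.062 |
| 0.1 | 0.7 | 0.10 | 0.113 | 0.07 | 0.086 |
| 0.2 | 0.5 | 0.20 | 0.205 | 0.10 | 0.100 |
| 0.2 | 0.7 | 0.20 | 0.309 | 0.14 | 0.198 |

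The nominal error is 0.05. A bias of 0.1 SD is 0.1/0.5 = 20% of the planned effect. The biases are absolute values; the sign depends on which arm is rated higher at baseline.

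**4. When the shift does not matter.** If knowing the arm moves ratings by the same amount s before and after, the change contrast is s − s = 0 and no bias arises.

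**The case against.** A reader might infer that patients and ward teams are told the arm before the baseline and that the baseline is therefore unblinded. The document does not establish this. The time of disclosure is not given, and that the SDAS raters belong to the informed clinical teams is likely but not stated. The flow diagram (Fig. 3) was not available, and a journal article condenses the full protocol. This stands: the order of randomisation is in the text, while the unblinding is an inference from the absence of any concealment.

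It is equally tempting to say that any arm-related shift passes in full into the effect, and in favour of VRAPT. Neither follows. Full transfer needs an unadjusted change contrast and a shift confined to baseline, and a constant shift cancels. Patients disappointed at having to wait could score higher at baseline, which would work against VRAPT.

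The strongest objection concerns the remedy. If ward staff are unaware at baseline and aware afterwards, a rating shift that would otherwise be constant, and so cancel, now enters the change contrast. That is correct. However, cancellation needs the shift to be equal in every period, and nothing in the plan secures this. A baseline free of knowledge of the arm is at least a sound reference, and what remains is the familiar limitation of unblinded outcome rating. Neither order removes that limitation.

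The illustration uses a two-point comparison and the plan a multilevel model with covariates, so the error rates show scale and do not predict this trial's results.

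**Conclusion.** The point holds in limited form. By the written order, the baselines of both primary measures are post-randomisation, and nothing in the document keeps the arm from patients or raters while these baselines are collected. They may therefore be unblinded. A baseline shift that does not persist would bias the group x time effect, in a direction the document does not determine. On the assumptions shown, a shift of 0.1 SD takes the 5% error to about 9-11% for a change contrast and about 6-9% with baseline adjustment; a shift of 0.2 SD takes it to about 20-31% and 10-20%. Adjustment reduces the problem but does not cure it.

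The random allocation itself remains valid and the sample size is unaffected. Balance checks on socio-demographic variables keep their meaning; those on SDAS and AVL do not. The trial is listed as ongoing, so later enrolments can still be protected.

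**What to change.** **Patients still to be enrolled.** Randomise only after the 12-week SDAS baseline and T1 are logged. Alternatively, keep the present draw but have the research coordinator release the allocation only at that point. State the time of disclosure in the protocol. The cost is a procedural amendment and shorter notice for scheduling trainers; no extra patients, visits or staff are needed.

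**Patients already allocated.** Record the date on which the patient and the ward team learned the arm. Add a sensitivity comparison of post-intervention SDAS and AVL levels between arms that does not use the baseline. Randomisation supports this comparison, at some cost in precision: with 64 per arm its SE is √(2/64) = 0.177 SD, against 0.126 to 0.153 SD with baseline adjustment at the correlations assumed above. Describe baseline SDAS and AVL differences in these patients as possible consequences of allocation.

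**Analysis.** A mid-trial change leaves two baseline regimes in one data set. Report results by regime, before and after the change.

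**Limitation to state.** None of this removes unblinded SDAS rating during and after the intervention. The protocol should acknowledge it.

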**Fig. 3 Fig3:**
[figure not shown]
CONSORT Flow Diagram

### Randomization

Participants will be randomly assigned to one of two conditions: VRAPT or waiting list. Randomization is conducted via a scientific randomization program on the Internet (https://www.randomizer.org), by the research coordinator of the Department of Psychiatry from the University Medical Center Groningen. Twenty-two sets consisting of two unique numbers are made available for each participating FPC. Research assistants are informed about the randomization by e-mail and communicate the condition verbally to the participants and the clinical teams.

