**Methods:**

Four forensic psychiatric centers in the Netherlands are participating in this study. Participants will be randomly assigned to either VRAPT or a waiting list. The two groups will be compared at several different time points: baseline (12 weeks before intervention), pre-intervention, post-intervention and at 12 weeks follow-up. After follow-up measurements are completed, participants from the waiting list will also receive VRAPT. The primary outcome is level of aggressive behavior, consisting of staff-reported and self-reported measures. Secondary outcomes are self-report questionnaires on e.g., anger, impulsivity and aggression.

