### Power and sample size calculation

There is no previous research using VR aggression regulation training in patient forensic populations based on which an effect size could be estimated. Conventional aggression regulation therapy in such settings has an effect size of around 0.3 [18]. An effect size of 0.5 is considered as moderate. Using this effect size with a β-power of .80, alpha of .05 and an independent two-sided t-test to evaluate the main outcome, 64 subjects are required in each condition, total *N* = 128.

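### Pairs of two within each centre, with each result told to the staff who refer and invite, make up to half of the allocations predictable

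*Protocol article*

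**What the plan says.** The Randomization section gives the scheme in a few sentences. "Participants will be randomly assigned to one of two conditions: VRAPT or waiting list". The research coordinator of a university psychiatry department draws the numbers with a web-based randomiser, and "Twenty-two sets consisting of two unique numbers are made available for each participating FPC". On disclosure, "Research assistants are informed about the randomization by e-mail", and they then tell participants and clinical teams the condition.

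Other sections show who selects patients. Under Inclusion criteria, the treatment supervisor and/or clinical team refers patients, partly on current problems with reactive aggression. Under Procedure, treatment supervisors screen, and "Patients who meet inclusion criteria are invited by an independent research assistant to participate". Patients then have one week to decide, give written consent and are allocated. The 12 weeks of baseline staff observation with the SDAS follow allocation.

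On size, the sample size section states that "64 subjects are required in each condition, total *N* = 128", and the abstract states that "Four forensic psychiatric centers in the Netherlands are participating in this study".

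**The concern.** A set of two numbers for two arms at 1:1 leaves one place for each arm, so the first allocation in a set fixes the second. This is the smallest possible 1:1 block and the most predictable. It would matter less if those who choose patients did not learn earlier results. Here the research assistants and clinical teams are told every result, and the Waiting list section says that both conditions may live on the same ward. The section mentions neither varying set sizes nor keeping the set size from the centres.

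At stake is the comparability of the arms at entry. Referral rests on clinical judgement, and supervisors may override a documented IQ below 70. The Discussion says that engaging these patients is challenging and that attrition is high. Staff who expect the next place to be VRAPT could put forward a willing patient, and hold that patient back when the next place is the waiting list. Motivation plausibly affects both staff-rated and self-reported aggression. The planned baseline comparisons and covariates act on measured characteristics only. Intention-to-treat analysis does not help, because this selection happens before randomisation.

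**Working it through.** **Inputs from the protocol article.** Two arms; 22 sets of two numbers per centre (Randomization); four centres (abstract); 64 per condition, 128 in total (Power and sample size calculation).

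**The plan's own figure.** For a standardised difference of 0.5, two-sided alpha 0.05 and power 0.80, the t-test solution is 63.77 per arm, rounded up to 64, with power 0.801. The stated 128 is reproduced, and the point below does not change it.

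**Places available.** 22 × 2 = 44 per centre, and 44 × 4 = 176 in all, against 128 needed. If recruitment is equal (an assumption), that is 128 / 4 = 32 patients, or 16 pairs, per centre.

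**Predictability of a block of two.** The first place is a fair coin and the second is determined.

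- Determined share: 1/2, that is 64 of 128 planned allocations (22 of 44 places in each centre's list).
- Expected correct guesses: (0.5 + 1) / 2 = 0.75, against 0.50 for unpredictable allocation.

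**Larger blocks, for comparison.** For a known block of 4, the six possible orders contain on average (2 × 2 + 4 × 1) / 6 = 1.33 determined places, and 1.33 / 4 = 33%. Correct guesses are (1/2 + 2/3 + 2/3 + 1) / 4 = 0.708. The same enumeration gives the other rows.

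| Block size, known to the recruiter | Determined | Correct guesses |
|---|---|---|
| 2 | 50% | 75% |
| 4 | 33% | 71% |
| 6 | 25% | 68% |
| 8 | 20% | 67% |

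**Undisclosed mix of 4 and 6.** In a simulation with 32 patients per centre and a recruiter who always guesses the arm that is behind, about 69% of guesses are correct. The fall from 75% is therefore about 6 percentage points. The larger gain is in certainty. A recruiter who does not know where a block ends can rarely be sure of the next place, whereas with pairs every second place is certain.

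**Cost in efficiency.** The largest imbalance within an unfinished block of 6 is 3. Relative efficiency at 32 per centre is 1 − (3/32)² = 0.991, a loss of about 0.9%.

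**The case against.** A reader might go further and infer that allocation is not concealed at all, or that every second allocation is in fact known before the patient is approached. The article does not support either reading. The sequence is generated centrally, allocation follows written consent, and the first place in each pair remains a fair coin. Foreknowledge of the second place needs three things the article does not state: that staff know or work out the pairing, that patients are allocated one at a time, and that the first result of a pair is out before the next patient is approached. With a week for each patient to decide, several may be pending together, and the text does not exclude allocating both members of a set at once. The article does not use the word block, so the pairing is itself an inference. Who physically holds the list is also not settled, and that is a detail an article may leave to the full protocol.

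Other text limits the scope for steering. All eligible patients are to be asked, so the discretion lies mainly in order and timing. The inviting assistant is described as independent. Waiting-list patients receive VRAPT after follow-up, which weakens the motive. The covariates in the model can absorb part of any imbalance in measured risk factors.

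These points reduce the claim from certainty to risk, but they do not remove it. Order and timing are enough to exploit a known next place. The independent assistant receives every result. A pattern in which every pair splits one to each arm is easy to notice over 16 pairs. Covariates do not reach unmeasured motivation. Nor is this a gap that a fuller document would fill, because the article itself states the set size.

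**Conclusion.** The point holds as a risk of selection bias, not as a demonstrated failure of concealment. On the natural reading of the Randomization section, up to half of the allocations (64 of 128) can be deduced by anyone who knows or infers the pairing, with 75% expected correct guesses. It rests on three assumptions: that each set holds one place per arm, that patients are allocated one after another, and that earlier results reach the staff who refer and invite. The last follows from the article; the first is the natural reading of it, and the second is not stated. The direction and size of any resulting bias in the treatment effect cannot be derived from the article. The change should be made: it is a cheap improvement to a trial that the article describes as ongoing.

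**What to change.** For all patients not yet randomised, replace the sets of two with permuted blocks of randomly mixed size (for example 4 and 6) within each centre. The research coordinator should generate and hold the list, release one allocation at a time after written consent, and not disclose the block sizes to the centres. Randomisation should stay before the 12-week SDAS baseline, as the Procedure section has it. Making release wait for the baseline data would delay randomisation by about 12 weeks and change the design.

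The cost is a new list, with no added patients or visits. Imbalance can reach 3 patients per centre, which is about 0.9% of efficiency if a centre recruits about 32 (an assumption; the article does not give recruitment by centre). Two limits should be stated openly: correct guesses remain at about 69%, and patients already allocated are not protected. The number still to be randomised is not given.

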## Design/methods

### Design

The study is a single blind randomized controlled trial (RCT) with two conditions: (I) the VRAPT condition, in which participants receive the VR training in addition to treatment as usual (TAU) and (II) the waiting list. Participants on the waiting list receive TAU only and are placed on a waiting list to receive VRAPT after the follow-up measurements have been completed. Participants in both conditions are not allowed to participate in any other therapies or trainings specifically focusing on aggression regulation during the research period. The two conditions are compared at four different periods in time. First, a period of 12 weeks staff observations before intervention (baseline), pre-intervention (T1), post-intervention (T2), and after 12 weeks of staff observations a follow-up (T3). The waiting list is offered VRAPT after the end of T3.

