### Measurement instruments

#### Primary outcome

##### Level of aggressive behaviour

Primary outcome measure is level of aggressive behaviour. Self-report questionnaires and staff-reports are used to assess the effectiveness of VRAPT, because the perspectives of patients and staff represent distinct but complementary measures of aggressive behaviour.

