##### Aggression questionnaire (AVL)

In addition, participants are asked to the Dutch version of the Aggression Questionnaire (AVL; [22]) at three different measuring points: pre-intervention (T1), post-intervention (T2), and 12-week follow-up (T3). This questionnaire assesses four sub traits of aggression, i.e., physical aggression, verbal aggression, anger and hostility [23]. The test–retest reliability of the AQ total scores were good and validity showed significant correlations with alternative aggression measurements. A Dutch study showed good internal consistency (Cronbach’s α (total, inpatients) = .83; [24]).

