##### Interview

At follow-up, patients in the VRAPT condition will be interviewed by the research assistant to assess their own opinion about VRAPT. Questions such as: “how did VRAPT contribute to your personal aggression management?” will be asked. This will contribute to the secondary outcome measures, as specific questions about VRAPT can be asked in addition to the self-report questionnaires.

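### The single-blind label covers only the staff who guide the questionnaires; as described, neither primary outcome (AVL, SDAS) is protected from knowledge of the arm

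*Protocol article*

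**What the plan says.** The Design section of the protocol article states: "The study is a single blind randomized controlled trial (RCT) with two conditions". It does not say there who is blinded.

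The Randomization section sets out how the allocation is passed on: "Research assistants are informed about the randomization by e-mail and communicate the condition verbally to the participants and the clinical teams".

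The primary outcome, under Level of aggressive behaviour, has two sources: "Self-report questionnaires and staff-reports are used to assess the effectiveness of VRAPT". The staff part is the weekly SDAS. According to the Procedure section, "During the intervention, aggression keeps being monitored with the SDAS by staff working on the ward". The self-report part is the AVL, which the participant completes at pre-intervention, post-intervention and follow-up.

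One blinded role is described. The Procedure section says that the self-report measures repeated after the last session are "guided by assessors who are blinded for treatment allocation". The same section places random allocation before the 12 weeks of SDAS baseline observation. The section on the waiting list says that patients from both arms may live on the same ward.

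**The concern.** A reader who meets the single-blind label will assume that it protects the outcome on which the trial is judged. The stated procedure tells the arm to the person who answers one primary instrument and to the teams around the people who rate the other. The blinded assessors guide the completion of questionnaires. They do not answer the AVL and do not score the SDAS.

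This matters more for the SDAS than for the AVL. A patient cannot be kept unaware that he is receiving a virtual reality training rather than waiting for one, so an unblinded AVL is unavoidable in this design. The staff rating is the natural check on the self-report, and the Discussion presents it that way. SDAS items such as irritability and negativism require judgement, and the article reports moderate inter-rater reliability (together with good convergent validity). If raters who know the arm expect the training to help, their scores can move in the direction of the hypothesis, and a larger sample would not remove that.

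**Working it through.** **Step 1. Who knows the arm, by outcome**

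| Outcome | Who supplies the score | Told the arm? | Covered by the stated blind? |
|---|---|---|---|
| AVL | Participant | Yes (Randomization) | No; the assessor who guides completion is blinded, the respondent is not |
| SDAS | Staff working on the ward | Clinical teams are told (Randomization); overlap with the raters is very probable but not stated | No; no blinded or independent rater is described |

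The blind thus covers how the self-report questionnaires are administered and nothing else.

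**Step 2. When the arm can be known.** Allocation precedes the 12-week SDAS baseline, so the arm may be known during the baseline ratings as well. The Statistical analysis section tests group-by-time interactions. Write the rating bias as b0 during baseline and b1 after the intervention starts. A bias that is constant over time (b1 = b0) falls into the group effect and cancels from the interaction. The interaction is shifted by b1 − b0. Expectations about a training plausibly change when the training begins, so b1 − b0 need not be zero.

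**Step 3. The plan's own figure.** Inputs from the power section: effect 0.5 SD, power 0.80, two-sided alpha 0.05, independent t-test. The noncentral t calculation gives 63.77, rounded up to 64 per arm, with power 0.801. The stated 64 per arm (128 in total) is reproduced and is not in dispute.

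**Step 4. Illustration of size.** Assumptions: no true effect, 64 per arm, one comparison of post-intervention means, and a shift b (in SD) caused only by knowledge of the arm. The values of b are not in the document.

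- Standard error of the difference: sqrt(2/64) = 0.177 SD.
- Probability of a significant result: Φ(b/0.177 − 1.96) + Φ(−b/0.177 − 1.96).

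| Assumed shift b (SD) | Normal approximation | Noncentral t |
|---|---|---|
| 0.1 | 0.087 | 0.087 |
| 0.2 | 0.205 | 0.202 |
| 0.3 | 0.396 | 0.392 |

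Rounded, these are about 9%, 20% and 40%, against a nominal 5%. All three shifts are smaller than the 0.5 SD the trial is designed to detect.

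**The case against.** The other side has a fair case on several points.

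- **The label has a basis.** One role is blinded, the Procedure section names it, and the Randomization section is open about who is told. A careful reader can work out what the blind covers. This stands in part: the label is loose and unqualified rather than invented.
- **The SDAS raters are not said to be told.** One section speaks of clinical teams, another of staff on the ward. A reader might take it as established that every rater is informed of the arm; the document does not say so. The overlap remains a strong inference, because no step keeps raters unaware and both arms can share a ward.
- **The assessor blind is not shown to be broken.** A reader might infer that it fails because the presence questionnaire (IPQ) is given at post-intervention, or because "patients in the VRAPT condition will be interviewed by the research assistant". The document does not support this. The blinded session repeats the pre-intervention measures; in Table 1 the IPQ is not one of them, and who gives it is not stated. Research assistants, who receive the allocation, and blinded assessors read as separate roles.
- **The rates are illustrative.** The shifts are assumed, and the planned analysis is a multilevel repeated-measures model, not a single comparison of means. Under that model only a bias that changes over time matters. That staff expectation favours the training is plausible but undocumented. All of this stands, and the rates must be read accordingly.
- **A remedy is only partial.** The AVL cannot be blinded against a waiting list, patients may tell staff their arm, and the Trial status section says the trial is ongoing.

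None of this removes the core. Telling the arm to the clinical teams is a stated procedure, not a detail left to a fuller document.

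**Conclusion.** The point holds in this form: the blind described protects neither primary outcome. That is certain for the AVL, whose respondent is told his arm. For the SDAS it is very probable, and rests on the inference that the clinical teams include ward raters. The unqualified single-blind label therefore suggests more protection than the procedure gives.

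The size cannot be determined from the document. The figures of about 9%, 20% and 40% show how quickly the error rate would rise for shifts of 0.1 to 0.3 SD under the simple comparison; they do not estimate this trial's false-positive rate. What enters the planned test is the change in bias after the intervention starts. The document does not support going further and calling the label false or the assessor blind broken.

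**What to change.** 1. **Randomization section, for participants not yet allocated:** tell the arm only to the participant, the trainer, the treatment supervisor and whoever schedules the sessions. Do not announce it to the staff who score the SDAS.
2. **SDAS form:** add one item recording whether the rater knows the arm, and report a sensitivity analysis by rater awareness. Awareness arises after randomization and may differ between arms, so this analysis shows how exposed the result is; it does not correct it.
3. **Design section and trial reports:** replace the single-blind label with a statement per outcome: AVL unblinded (self-report); SDAS not reliably blinded; only the assessors who guide the questionnaires blinded.

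The cost is one changed line of communication, one tick-box and a few words of text. Sample size and visits are unaffected. There are downsides. Some ward staff will still infer the arm. Because the trial is ongoing, earlier and later participants may have been rated under different disclosure practices, which the awareness record helps to show only from the time it is introduced. The blinding claim also becomes less favourable. If wards must know the arm for practical reasons, items 2 and 3 can still be done.
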